### 9.1.2 STAGE 2 Safety and Tolerability Study

In accordance with the intent-to-treat principle, all subjects randomized will be kept in their originally assigned treatment group for analysis. All randomized subjects will be considered evaluable for tolerability and safety. In the tolerability analyses, subjects will be regarded as a treatment failure if they fail to complete Week 20 of the study on the originally assigned treatment for any reason. The decision will also involve the result of the pharmacokinetic study, since we wish to choose a dosage where the trough levels are greater than  $1\mu\text{M}$ . We consider several possible scenarios, and the decision rules that might be used. The data will be reviewed

by the Steering Committee, using the considerations here as guidelines. Their recommendation would then be reviewed by the DSMB.

We will consider a dosage tolerable if the proportion of treatment failures for a dosage is less than 40% with 80% confidence. With 20 subjects this would occur if 5 or fewer subjects fail to complete the 20-week study. With 20 subjects we will have more than an 80% chance of declaring a dosage tolerable if the true treatment failure rate is 20%. If both dose regimens are tolerable and both achieve 1 $\mu$ M and there are no serious dose related adverse events on the higher dosage and no differences at the one-sided  $p=0.10$  level between adverse event rates that are deemed important then we will use the twice a day dose for the remainder of the study. This would also be the regimen of choice if the one a day regimen did not achieve 1 $\mu$ M and the twice a day regimen was tolerable. Otherwise, we would choose the once a day regimen if it were tolerable and achieved 1 $\mu$ M. If the regimen that achieved 1 $\mu$ M was not tolerable or no regimen achieved 1 $\mu$ M we would consider ending the trial. The decision at this point might involve knowledge of the other pharmacokinetic parameters since if the average dose is high enough it may be worthwhile to continue. In addition we may find that we have equivocal data on the tolerability of whatever regimen achieves 1 $\mu$ M. This would require us to continue the second stage of the study beyond 60 subjects. For instance this might happen if 5-10 subjects in the dosage that achieved 1 $\mu$ M did not tolerate therapy or we had to make substantial changes in the protocol during the first 20 weeks.

An additional purpose of the STAGE 2 study is to determine serious adverse effects of treatment while the study is being conducted by only a few centers. With 20 subjects we will have an 80% chance of seeing at least one occurrence of any adverse event that occurs with a frequency of 8% or more.

### ***9.1.3 STAGE 3 Efficacy Trial***

There will be two co-primary endpoints, survival and ALSFRS-R. Both survival and ALSFRS-R endpoints will be tested using a p-value of 0.05, as discussed in O'Brien [186]. We have chosen not to use an explicit p-value adjustment for these two co-primary endpoints. We are considering the question of whether Ceftriaxone preserves functional outcome (ALSFRS-R) and whether it improves survival as separate questions.

#### ***Analysis of Survival***

The primary analysis will be by "intention to treat." We will ascertain the status of all subjects at the end of the study and every subject will be included in the analysis whether or not they elected to stop treatment before the end of the study. The analysis of survival will use a log-rank test stratified by riluzole use.

A sample size of 600 subjects will provide us with over an 80% power to detect a 50% increase in median time to death, tracheostomy or PAV, from 29 months to 44 months for subjects taking the drug. In terms of the one-year survival rate this would be a change from a 75% one-year rate to an 83% one-year rate, or a change from a 24% five-year rate to a 38% five-year rate for patients taking the drug.

The trial will be monitored every six months for efficacy and futility. Stopping for efficacy will only occur if the survival comparison exceeds boundaries described below. Decisions on futility will depend on both primary endpoints, as well as the realized accrual of subjects into the study and the frequency of subjects discontinuing study medication.

Since there are a very large number of sites that will be enrolling subjects, there will not be sufficient power in the study to examine the effects of each site individually.

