## 2 BACKGROUND AND SIGNIFICANCE

### 2.1 Background and Rationale

#### 2.1.1 *Clinical Features and Epidemiology of ALS*

Amyotrophic lateral sclerosis is a rare degenerative disorder of large motor neurons of the cerebral cortex, brain stem and spinal cord that results in progressive wasting and paralysis of voluntary muscles [7]. The incidence of ALS is currently approximately 2/100,000/year [8, 9] and may be increasing [10]. The lifetime ALS risk is 1 in 600 to 1 in 1000. Even though the incidence of ALS is similar to that of multiple sclerosis [11], the prevalence is only 4-6/100,000 (about 25,000 patients in the United States), due to the higher mortality rate. Fifty percent of ALS cases die within three years of onset of symptoms and 90% die within five years [11]. The median age of onset is 55 years. The cause in most cases is unknown. Age and gender are the only risk factors repeatedly documented in epidemiological studies [12]. There is a slight male predominance (3:2 male to female ratio) in sporadic ALS. No treatment

prevents, halts or reverses the disease, although riluzole use is associated with a slight prolongation of survival [13, 14].

The majority of ALS cases are sporadic (SALS); 10% are familial (FALS). More than 100 point mutations in the gene encoding cytosolic copper-zinc superoxide dismutase (SOD1) have been demonstrated to cause typical FALS [15]. Essential features of ALS are progressive signs and symptoms of lower motor neuron dysfunction (atrophy, cramps, and fasciculations) associated with corticospinal tract signs (spasticity, enhanced and pathological reflexes) in the absence of sensory findings [9]. There is relative sparing of muscles of eye movement and the urinary sphincters. The course is relentless with decline in strength, respiratory function and overall function with time during the active phase of the disease [16]. Natural history studies have determined that age at onset, site of onset, delay from first symptom to entering ALS clinic, and rate of change in respiratory function are significant covariates of survival [17-20]. No study has correlated activity of any surrogate marker with the extent of motor neuron loss as detected by post-mortem examination.

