Survival in patients with ALS is affected by many factors in addition to disease modifying therapy. Nutritional issues, including timing and acceptance of gastrostomy tube are clearly important. No clear data currently exists regarding the extent to which gastrostomy tube placement prolongs survival, although current practice parameters suggest that gastrostomy should be considered before pulmonary function is clearly compromised [154]. Studies to determine the effect of gastrostomy on survival are in progress; however, it seems clear that quality of life is improved with appropriate placement [155-158]. Lacking data on the beneficial effect of gastrostomy tube placement on survival, site investigators will be asked to follow the AAN Practice Parameters. Similarly, although no large prospective trial has been performed, several small prospective and retrospective studies suggest that use of non invasive positive airway pressure ventilatory support prolongs survival in ALS patients [159-161]. For this reason, investigators will be asked to follow the practice parameter referenced above for non-invasive ventilatory support as well. Other factors influence survival in patients with ALS,

including age at diagnosis and site of onset [162-165]. In this study, we will not formally stratify for such variables, but will expect that randomization will result in equal distributions of sex and site of distribution, as has occurred in prior studies. We expect that the randomization will balance ancillary treatments among the treatment groups.

There will be two primary endpoints, survival and ALSFRS-R. There are several reasons for supporting two primary endpoints. First, survival requires long duration of study, and we are concerned with potential drop out with a long study. ALSFRS-R potentially is amenable to alteration over a significantly shorter period, so that late dropouts would have much less of an adverse effect on this measure. Secondly, we are powered to detect a smaller difference in disease progression for ALSFRS-R as compared to survival. We wish to maintain survival as a co-primary endpoint as we believe that ultimately this is the most meaningful endpoint for patients. Subjects who discontinue drug late in the study may still provide valuable data in a survival analysis as long as their survival is tracked. Using co-primary endpoints does not come at a great cost of power for either endpoint. Equal emphasis on both measures is appropriate.

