### ***Stopping for Efficacy***

Efficacy stopping will use the alpha spending rule approach which allows flexible choice of monitoring times. The basic idea is that the trial can “spend” (or allocate) a one-sided Type one error of 0.025 (equivalent to a two-sided  $p=0.05$  test) over the course of the trial. Thus one can pre-define a “spending” function which gives the amount of alpha spent as a function of the proportion of the total number of events that have occurred by the time of the interim analysis. We will schedule the interim analyses as defined below with an alpha spending function which depends on the proportion of events, denoted by  $t$  (so called information time), that has occurred by that analysis. The alpha spending function we will use is  $0.025 t^3$ . We will assume that the total number of events on the trial will be 293, this is the number expected based on a yearly survival rate of 75%, for the purposes of computing  $t$  although this may be adjusted using the guidelines in Proschan, Lan and Wittes [187]. The table below gives the efficacy stopping guidelines for the trial based on our assumptions about the accrual and mortality rate. The two event rate estimates are calculated under the alternative and null hypothesis assuming a one year survival of 75%. We assume that the accrual will take five months to ramp up to 25 patients per month. The  $p$ -value to stop is one-sided. The first meeting three months after the start of accrual for STAGE 3 (Study Month 3) will have the purpose of reviewing the safety of Ursodiol use and any other new procedures of the STAGE 3 portion of the study.

| Study Month | Accrual | Number of Events | $p$ -value to stop |
|-------------|---------|------------------|--------------------|
| 3           | NA      | NA               | NA                 |
| 9           | 235     | 31-40            | 0.000064           |
| 15          | 385     | 61-75            | 0.000374           |
| 21          | 535     | 102-125          | 0.001686           |
| 27          | 600     | 153-187          | 0.005537           |
| 33          | 600     | 201-244          | 0.011807           |
| 39          | 600     | 243-293          | 0.019872           |

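### The primary survival test adjusts only for riluzole; pre-specified adjustment for baseline predictors recorded at screening could add roughly 1 to 8 points of power at little cost

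*Combined protocol and SAP*

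**What the plan says.** Section 9.1.3 (Analysis of Survival) sets the primary test: "The analysis of survival will use a log-rank test stratified by riluzole use". Section 6.3.4 (STAGE 3) repeats it. The test level is given in 9.1.3: "Both survival and ALSFRS-R endpoints will be tested using a p-value of 0.05". The monitoring plan spends a "one-sided Type one error of 0.025" over the trial.

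The power statement reads "A sample size of 600 subjects will provide us with over an 80% power to detect a 50% increase in median time to death", where the endpoint also counts tracheostomy and PAV. The effect is then put as medians moving "from 29 months to 44 months for subjects taking the drug", and on the one-year scale as "a change from a 75% one-year rate to an 83% one-year rate".

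On predictors, section 2.1.1 lists "age at onset, site of onset, delay from first symptom to entering ALS clinic" and the rate of change in respiratory function as significant covariates of survival. Section 3.1 describes the ALSFRS-R as closely correlated with survival. Section 6.3.4 adds that age at diagnosis and site of onset influence survival, then states: "In this study, we will not formally stratify for such variables, but will expect that randomization will result in equal distributions".

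On availability, VC and ALSFRS-R are measured at the screening visit (Screening and Informed Consent). Age and time since first symptom are needed to apply the inclusion criteria in 4.1. Site of onset is not listed explicitly as a screening item.

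Riluzole is a randomization stratum (Précis, Randomization; 4.3.4). The description of the ALSFRS-R shared-parameter model in 9.1.3 mentions no riluzole term.

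**The concern.** When baseline factors that drive survival are left out of a survival comparison, two things follow even in a properly randomized trial. First, the hazard ratio averaged over a mixed population lies closer to 1 than the ratio among comparable subjects, so the unadjusted test is less sensitive than it could be. This happens under perfect balance. Second, randomization balances predictors only on average, and an unadjusted test does not correct the imbalance that occurs in the one trial that is run.

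The reason given in 6.3.4 answers neither point. It is also a reason for not stratifying the randomization, which is a separate decision from which covariates enter the analysis. At stake are a few points of power on a co-primary endpoint, and protection of the main survival result against chance imbalance in factors the protocol itself considers prognostic.

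**Working it through.** **1. Reproduce the plan's power.** Inputs from 9.1.3: 75% one-year placebo survival, a 50% increase in median, 243 events expected under the alternative at month 39 (293 under the null), and a final one-sided boundary of 0.019872. Allocation is 2:1 (Précis).

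- Exponential check: hazard = −ln(0.75)/12 = 0.02397 per month. The medians are 28.9 and 28.9 × 1.5 = 43.4 months. One-year survival on drug is 0.75^(1/1.5) = 82.5%. Five-year rates are 23.7% and 38.3%. All agree with the protocol's rounded figures.
- Schoenfeld formula: power = Φ(√(d × 2/3 × 1/3) × ln HR − z).
- With d = 243 and HR = 1.5: √54 × 0.4055 = 2.980. At z = 1.960, power = Φ(1.020) = **84.6%**. At the final boundary, z = 2.056 and power = Φ(0.923) = **82.2%**.
- Events for 80% power: (1.960 + 0.842)² / (2/9 × 0.4055²) = 215.

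The claim of over 80% therefore holds.

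**2. What adjustment would add.** The documents give no prognostic strength, so it is an assumption: a normal baseline score on the log-hazard scale with SD 0.3, 0.5 or 0.7 (C-index about 0.59, 0.64 and 0.68). Each simulation used 4,000 trials per setting, 400:200 allocation, the protocol's accrual (five-month ramp to 25 per month), a month-39 cut-off and 75% one-year placebo survival. The log-rank test without the score and the Cox test adjusted for it were applied to the same data. Riluzole strata were not simulated. Simulated events averaged 221–234.

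If 1.5 is the hazard ratio among subjects with the same score (conditional), power at two-sided 0.05 is:

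| SD | Unadjusted HR | Log-rank | Adjusted | Gain (points) |
|---|---|---|---|---|
| 0.3 | 1.48 | 82.6% | 84.0% | 1.4 |
| 0.5 | 1.46 | 79.8% | 83.6% | 3.8 |
| 0.7 | 1.44 | 75.9% | 83.5% | 7.6 |

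If about 1.5 is the population-average (marginal) hazard ratio, the conditional value is 1.517, 1.545 and 1.58 respectively:

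| SD | Log-rank | Adjusted | Gain (points) |
|---|---|---|---|
| 0.3 | 85.6% | 87.6% | 2.0 |
| 0.5 | 85.6% | 88.7% | 3.1 |
| 0.7 | 84.1% | 91.0% | 6.9 |

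At the final boundary of 0.019872 the gains run from 1.1 points (80.6% to 81.7%) to 8.3 points (72.8% to 81.1%). The Monte Carlo standard error of one power figure near 80% is √(0.8 × 0.2/4000) = 0.6 points.

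**3. Which SDs fit the protocol's survival figures.** With a constant hazard given the score, placebo survival is S(t) = E[exp(−λ·e^x·t)], where x is the score and λ is set so that S(12) = 75%. The protocol states a 29-month median and 24% at five years.

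| SD | Implied placebo median (months) | Implied five-year survival |
|---|---|---|
| 0.3 | 29.5 | 25% |
| 0.5 | 30.5 | 28% |
| 0.7 | 32.1 | 31% |
| 0.8 | 33.2 | 33% |
| 1.0 | 35.9 | 37% |

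Agreement worsens steadily as the SD rises. SD 0.7 is already at the upper end of what is plausible here, and larger values should not be used to size the gain.

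**The case against.** The planned test is valid, is stratified by a randomization factor, and meets its stated power. Section 6.3.4 shows that not stratifying was a deliberate choice. All of that stands, and it is why this is an improvement and not a correction.

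A reader might infer that the survival comparison is underpowered, since the conditional table shows the log-rank test at 79.8% and 75.9%. The documents do not support that. Section 9.1.3 defines the effect by population medians and one- and five-year rates, and calls the hazard ratio an intention-to-treat value for all participants combined. Those are marginal quantities, and on that reading the log-rank test keeps 84–86%. The shortfall is relative to what adjustment could achieve, not to the protocol's claim.

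A reader might also infer that every named predictor is strong and already in hand. The protocol calls them significant, not strong. The respiratory predictor it names is a rate of change, which a single screening VC cannot supply, and capture of site of onset needs confirming.

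Two further objections stand in part. The simulation adjusts for the true score; several covariates with estimated coefficients, uncertain functional form and some missing values would recover less. And the change is not free: interim efficacy and futility rules are written around survival p-values, and section 5.1.1 records that the DSMB and a few Steering Committee members have seen unblinded data on Stage 1 and 2 subjects who enter the Stage 3 analysis. That makes the timing and documentation of any change important. It is not a reason to forgo the change.

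**Conclusion.** The point holds as a low-cost improvement. The survival test leaves out baseline information that the protocol regards as prognostic and largely records, and the stated reason covers expected balance only. With the same subjects and events, adjustment would gain roughly 1–2 points of power if the baseline score is weak (SD 0.3), 3–4 if moderate (SD 0.5) and 7–8 if fairly strong (SD 0.7), whichever way the hazard ratio of 1.5 is read. The range rests on an assumed prognostic strength and on adjustment for the true score, so the upper figures are optimistic. The stated power is not wrong.

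**What to change.** Before any Stage 3 efficacy look:

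- Define the primary survival test as the treatment term of a Cox model stratified by riluzole, with age, months from first symptom, screening VC (% predicted) and screening ALSFRS-R as covariates. Add site of onset if the screening history captures it. State the functional form of each covariate and how missing values are handled.
- Use the same statistic at every interim efficacy and futility look. The interim text currently refers to a log-rank test without mentioning riluzole, so it needs aligning in any case.
- Keep the riluzole-stratified log-rank as a sensitivity analysis.
- Include riluzole, the randomization stratum, in the ALSFRS-R shared-parameter model.

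No subjects or visits are added. The costs are that the reported hazard ratio becomes conditional rather than marginal, that Stopping for Efficacy, Stopping for Futility and the Feasibility/Futility Targets must be reworded to match, and that the change must be dated and shown to have been made without reference to unblinded efficacy data.

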### ***Stopping for Efficacy***

Efficacy stopping will use the alpha spending rule approach which allows flexible choice of monitoring times. The basic idea is that the trial can “spend” (or allocate) a one-sided Type one error of 0.025 (equivalent to a two-sided  $p=0.05$  test) over the course of the trial. Thus one can pre-define a “spending” function which gives the amount of alpha spent as a function of the proportion of the total number of events that have occurred by the time of the interim analysis. We will schedule the interim analyses as defined below with an alpha spending function which depends on the proportion of events, denoted by  $t$  (so called information time), that has occurred by that analysis. The alpha spending function we will use is  $0.025 t^3$ . We will assume that the total number of events on the trial will be 293, this is the number expected based on a yearly survival rate of 75%, for the purposes of computing  $t$  although this may be adjusted using the guidelines in Proschan, Lan and Wittes [187]. The table below gives the efficacy stopping guidelines for the trial based on our assumptions about the accrual and mortality rate. The two event rate estimates are calculated under the alternative and null hypothesis assuming a one year survival of 75%. We assume that the accrual will take five months to ramp up to 25 patients per month. The  $p$ -value to stop is one-sided. The first meeting three months after the start of accrual for STAGE 3 (Study Month 3) will have the purpose of reviewing the safety of Ursodiol use and any other new procedures of the STAGE 3 portion of the study.

| Study Month | Accrual | Number of Events | $p$ -value to stop |
|-------------|---------|------------------|--------------------|
| 3           | NA      | NA               | NA                 |
| 9           | 235     | 31-40            | 0.000064           |
| 15          | 385     | 61-75            | 0.000374           |
| 21          | 535     | 102-125          | 0.001686           |
| 27          | 600     | 153-187          | 0.005537           |
| 33          | 600     | 201-244          | 0.011807           |
| 39          | 600     | 243-293          | 0.019872           |

For example, by month 15, the study should have accrued 385 subjects, and between 61-75 events (death/PAV) will have occurred. A log-rank test will be carried out to compare survival between the placebo group and group of treated subjects. If this log-rank test leads to a one-sided  $p$ -value of less than 0.000374 then the study can be stopped for efficacy.

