**Duration of Participation**

The total study length from first enrolled subject is approximately 59 months: 18 months enrollment for STAGE 1, 20 weeks of follow-up in STAGE 2, 24 months for subject recruitment for STAGE 3 and 52 weeks of additional follow-up. It will take approximately seven months for intermediate analyses.

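### The survival alpha-spending clock is set to 293 events, a no-effect count dated about three months after the study ends, and no rule says how the final analysis spends what is left

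*Combined protocol and SAP*

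**What the plan says.** In Section 9.1.3, Stopping for Efficacy, survival monitoring spends "a one-sided Type one error of 0.025" over the trial. The spending function is 0.025 times the cube of t, where t is the proportion of total events observed. The total is set this way: "We will assume that the total number of events on the trial will be 293, this is the number expected" at a yearly survival of 75%. The same sentence adds "although this may be adjusted using the guidelines in" a cited monitoring textbook. Each event range in the table runs from the count under the alternative to the count under the null. The last row reads "39 | 600 | 243-293 | 0.019872" (study month, accrual, events, one-sided p-value). Study months count from the start of STAGE 3 accrual.

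Three other statements bear on the final test:

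- Analysis of Survival claims "over an 80% power to detect a 50% increase in median time to death, tracheostomy or PAV" with 600 subjects.
- Duration of Participation in the Précis gives "24 months for subject recruitment for STAGE 3 and 52 weeks of additional follow-up". The Précis and Section 3.1 end the study 52 weeks after the last randomization.
- The opening of Section 9.1.3 says "Both survival and ALSFRS-R endpoints will be tested using a p-value of 0.05".

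No section says what boundary applies if the study ends with fewer than 293 events.

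**The concern.** A spending function releases the whole error rate only when t reaches 1. Here t reaches 1 at a count expected only if the drug does nothing, and at a date after follow-up has closed. At the real final analysis t is therefore expected to be below 1 under either hypothesis, and furthest below it when the drug works.

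The documents then support several different final thresholds for a co-primary endpoint, and nothing chooses among them. The strictest costs a substantial amount of power. The loosest, 0.05 two-sided with no allowance for the interim looks, exceeds the intended error rate. A choice made after the result is known would be hard to defend.

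**Working it through.** **Inputs**

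- Spending rule, denominator, event ranges and accrual (five-month ramp, then 25 per month): Stopping for Efficacy.
- Effect: a 50% longer median, so a hazard ratio (placebo/active) of 1.5. The rounded medians give 44/29 = 1.517.
- Allocation: 540 subjects at 2:1 (360:180), plus 60 at 1:1:1 with the active arms merged (40:20), so 400:200.
- Event rate: 75% one-year survival, taken as exponential.
- Assumption: the STAGE 1 cohort entered over 18 months, starting 24 months before STAGE 3 accrual. This placement is chosen because it reproduces the table.

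**1. Reproduce the table.** Recursive integration with t = (40, 75, 125, 187, 244, 293)/293 gives nominal p-values of 0.000064, 0.000374, 0.001686, 0.005537, 0.011808 and 0.019872. These match the printed values to within 0.000001, so the boundaries were built on the null counts.

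**2. Locate the study end.** The table has 535 subjects at month 21. The remaining 65 at 25 per month take 2.6 months, so 600 is reached at month 23.6 and follow-up ends at 23.6 + 12 = 35.6. Duration of Participation gives 24 + 12 = 36. Month 39 is 3 to 3.4 months later.

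**3. Events at the study end.** The accrual and event model gives 201–245 at month 33 (table 201–244) and 243–292 at month 39 (table 243–293). At month 35.6 it gives about 220 under the alternative and 266 under the null. Other assumptions about STAGE 1 entry and the end date move the 220 between 217 and 225.

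**4. Alpha released if 293 is not adjusted**

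- Study end, alternative: (220/293)³ = 0.423, and 0.025 × 0.423 = 0.0106, or 42% of the total.
- Month 39, alternative: (243/293)³ = 0.570, and 0.025 × 0.570 = 0.0143, or 57%.
- Study end, null: (266/293)³ = 0.748, and 0.025 × 0.748 = 0.0187.

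**5. Power.** The expected final Z is √(D × 2/3 × 1/3) × ln 1.5. For D = 220 this is √48.89 × 0.4055 = 2.84. With no interim looks, 2.84 − 1.96 = 0.88, which is 81% power. With looks at 31, 61, 102, 153 and 201 events and then the final one:

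| Rule at the final look | 220 events (study end) | 243 events (month 39) |
|---|---|---|
| 293 unadjusted | cumulative alpha 0.0106, nominal p 0.0073, power 68% | cumulative alpha 0.0143, power 77% |
| Printed p-values as they stand | nominal p 0.0199, power 79% | nominal p 0.0199, power 83% |
| All remaining alpha spent | nominal p about 0.024, power 81% | power 84% |

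With 217 to 225 events, the unadjusted rule gives 67% to 70%. With a hazard ratio of 44/29 it gives about 71%; the printed p-values then give about 82% (at 222 events) and full spending about 83%.

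**6. A plain 0.05 test at the end.** Five looks at the printed p-values followed by a final one-sided 0.025 test give a total one-sided error of about 0.028 at study end (0.029 at month 39).

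**The case against.** The strongest reply is that nobody would run the unadjusted rule. The text permits 293 to be changed, and it says the full one-sided 0.025 is available over the trial. Spending the remainder at the end fits both statements and gives about 81%, so the power claim is sound.

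The plan's worked example also points away from the strict reading. It applies the single printed value 0.000374 at month 15 across the whole range of 61–75 events. Used that way under the alternative counts, the printed column spends 0.0251 by month 39 with 83% power. Recruitment is also approximate and may be lengthened (Sections 4.3.1 and 6.3.4), so month 36 is not fixed. Finally, the 0.05 can be read as concerning only the two co-primary endpoints, with no instruction to ignore the interim looks.

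Most of this stands. The table contains no arithmetic error, and the plan does not direct an unadjusted 0.05 test. But the permission to adjust names no trigger, direction or decision-maker, and does not say that t becomes 1 at the end. The printed p-values, used at the protocol's own end with a hazard ratio of 1.5, fall just short of 80%. A later end does not rescue the unadjusted rule either: at 243 events it still gives 77%.

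A reader might infer that survival power simply is 68%, or that the final test always gets less than half its alpha. The documents do not support either. The 68% needs 293 to be left unadjusted, and the less-than-half figure applies at study end and becomes 57% at month 39.

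**Conclusion.** The concern holds as a missing final-analysis rule combined with a calendar mismatch. The denominator is a no-effect count dated about three months after follow-up ends, and the documents allow final one-sided thresholds of 0.0073, 0.0199, about 0.024 or 0.025 at about 220 events. A result with a one-sided p of 0.015 would fail under the first and pass under the other three.

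Power at a hazard ratio of 1.5 runs from about 68% (293 unadjusted) through 79% (printed values) to 81% (all alpha spent). Only the last delivers the stated figure at the protocol's own end, and it is the one the plan does not write down. Leaving alpha unspent is conservative for type I error. The risk of inflation comes only from a plain 0.05 test, and it is small (about 0.028 against 0.025).

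These figures assume exponential survival, the plan's accrual and event rates, and the STAGE 1 timing stated in the working. What the cited textbook prescribes is not in the documents and was not assumed.

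**What to change.** Make three changes in Section 9.1.3:

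1. State that the final survival analysis takes place at the protocol-defined study end, sets t = 1, and spends all remaining alpha, with the last boundary recomputed from the observed event counts.
2. Replace the month-39 row with the study-end analysis (about month 36, about 220–266 events) and its recomputed boundary.
3. State in the opening paragraph that survival is judged against that final boundary, within an overall two-sided 0.05.

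Replacing 293 with 220 as the denominator would be a mistake. The table's null count at month 33 is already 244, so t would exceed 1 at an interim look and leave no alpha for the final analysis. The 81% above keeps 293 for the interim looks.

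The cost is wording and a recomputed table, best settled before the first efficacy look at Study Month 9. No extra patients or follow-up are needed, and the stated power of over 80% can stay.
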